6. RISKS AND DISCOMFORTS

Previous experience, the non-invasive nature of the proposed study, and the close supervision of subjects at the study site will minimize the potential risks. The co-investigators have extensive experience performing the study procedures. Therefore, the anticipated risk to the subjects from these studies is minimal.

1. Oral glucose tolerance test: The glucose solution has a sweet taste that may be considered unpleasant and may be associated with nausea or, rarely, vomiting. Subjects will be monitored by trained personnel during the OGTT.

2. Blood collection: Blood draws may cause fainting, tenderness, hematoma formation, and rarely, infection. Sterilization of the skin and collection of blood by skilled nurses minimizes these risks.

3. Questionnaires: It may be tiring to fill out questionnaires, but the subject will be given as much time as needed to complete them. Also, a participant may feel uncomfortable answering questions of a personal nature, but subject can always choose not to answer any question.

4. Weight Loss: Weight loss may occur too rapidly resulting in weakness and fatigue; however, weight loss will be gradual and overseen by the lifestyle coach, a dietitian with training to minimize this risk.

5. Confidentiality: The Principal Investigator and her staff will take all reasonable measures to protect the confidentiality of each subject’s records and data. Subject data will be referenced by number only. Research data kept online will be kept secure and confidential through extensive password protection, username anonymity, and redirected emails. Data will be stored in RedCap.

c. Device complications/malfunctions: none

d. Psychosocial (non-medical) risks: none anticipated

e. Financial Risks: none

6.1 POTENTIAL BENEFITS

a. Potential benefits to participating individuals

No direct individual benefit is likely to come from participating in this study. This study will explore the hypothesis that a novel lifestyle intervention program modeled upon the DPP for overweight/obese postpartum women at elevated cardiometabolic risk can successfully affect healthy diet and physical activity habits leading to weight loss and possibly reduce the risk for future development of type 2 diabetes and cardiovascular disease in the study population. We believe that the importance of gaining this knowledge outweighs the minimal risk posed to the subjects. Some women in both groups may receive a diagnosis of type 2 diabetes during the study. They may consequently be able to receive earlier care for this condition than they would have otherwise.

b. Potential benefits to society

The successes and failures of this program will help identify the unique obstacles that enable and prevent this at-risk population from reducing their type 2 diabetes and cardiovascular disease risk through diet and physical activity regimens. Lifestyle intervention programs like the DPP remain an extremely effective treatment for reducing cardiometabolic risk in at-risk populations; however, they are time- and labor-intensive, making them difficult to translate/replicate in at-risk populations with unique time restrictions (like new mothers/mothers of very young children/women in the first year postpartum). Identifying alternative lifestyle programs that are effective in this population may be therapeutically useful in this large segment of the population at elevated risk.

Protocol Management: The studies will be conducted in the well-supervised CCTSI at the University of Colorado. The subjects will be under constant observation by skilled professionals highly qualified to perform the study procedures. Procedures will be terminated immediately if potentially serious side effects develop. In the event of adverse reactions, medical care will be immediately available.

Data Management: The original recording of an observation will be retained as the source document. The principal investigator will prepare and maintain complete and accurate study documentation in compliance with good clinical practice standards and applicable federal, state, and local laws, rules, and regulations. Study documentation shall be made available at the investigator’s site upon request for inspection, copying, review and audit at reasonable times by any regulatory agency. The investigator will promptly take any reasonable steps that are requested as a result of an audit to correct deficiencies in the study documentation. Data confidentiality will be maintained and regulations regarding access to data by those other than the study staff will be followed. All information will be entered into the study dataset by coded entry only. The code identification data will be kept in a locked file available only to the principal investigator unless requested by the appropriate regulatory authority. Local data will be stored and collected using RedCap.

Study data will be collected and managed using REDCap (Research Electronic Data Capture). REDCap is a secure web application designed to support data capture for research studies, providing user-friendly web-based case report forms, real-time data entry validation (e.g. for data types and range checks), audit trails and a de-identified data export mechanism to common statistical packages (SPSS, SAS, Stata, R/S-Plus). The system was developed by a multi-institutional consortium which includes University of Colorado–Denver and was initiated at Vanderbilt University. The database is hosted at the University of Colorado–Denver Development and Informatics Service Center (DISC), which will be used as a central location for data processing and management. REDCap data collection projects rely on a thorough study-specific data dictionary defined in an iterative self-documenting process by all members of the research team with planning assistance from the DISC. This iterative development and testing process results in a well-planned data collection strategy for individual studies. REDCap also includes a powerful tool for building and managing online surveys. The research team can create and design surveys in a web browser and engage potential respondents using a variety of notification methods. REDCap is flexible enough to be used for a variety of types of research and provides an intuitive user interface for database and survey design and data entry. ^[[50]](#endnote-50)^

Progress Reports: Annual progress reports will be submitted to the COMIRB describing all of the study activities.

a. Independent monitoring of source data: none

b. Safety monitoring: A physician reviews all laboratory results as they become available. A physician involved with the study is available by pager 24 hours/day seven days/week if any difficulties arise.

c. Outcomes monitoring: The Principal Investigator [name], will be responsible for reviewing and reporting all data and safety data within 24 hours of receipt. We will address abnormal lab values as follows:

1) Glucose, HbA1c: We will review subject data in accordance with the American Diabetes Association (ADA) guidelines for the diagnosis of diabetes. The following values at the specified timepoints throughout the study year indicate that the subject will need to repeat the abnormal test to confirm the diagnosis of diabetes:

For participants with a recent history of GDM who complete an oral glucose tolerance test: At the 6-week visit, if the subject has a fasting glucose value >126 or a 2-hour OGTT glucose value >200. The HbA1c value collected at the 6-week visit is exploratory and is not clinically used to diagnose diabetes at 6-weeks, given that the result will be affected by hyperglycemia during pregnancy.

For all other participants (who will not complete an OGTT):
At the 6 week visit, if the subject has a fasting glucose value > 126.

• At the 6-month and 12-month visits, if the subject has a fasting glucose value > 126 or if the HbA1c value is ≥6.5.

If two of the subject’s initial clinical tests exceed these values, they will be diagnosed with diabetes at that timepoint. If one of the subject’s initial clinical tests exceeds these values we will schedule a repeat fasting glucose, OGTT, or HbA1c. If the subject’s repeat test result exceeds these values, the subject will be diagnosed with diabetes. Subjects diagnosed with diabetes at the 6 week visit will be excluded from the study. If a subject is diagnosed with diabetes at any visit other than the 6 week visit, we will continue to follow them. This is to ensure that we can collect data on all randomized subjects, including body weight which is the primary outcome of the study. We will assist all subjects diagnosed with diabetes with a referral to an appropriate provider to manage their condition.

2. Fasting lipid profile:

Based on the 2013 ACC/AHA blood cholesterol guideline statins should be prescribed in patients without clinical atherosclerotic cardiovascular disease with a LDL-C above or equal to 190 mg/dL, if a subject has a LDL-C above 190mg/dL, the study physician will call the participant to let her know that her cholesterol level was elevated and that she should contact her PCP. If a subject has a fasting TG level above 800 mg/dL, the study physicianwill call the participant to let her know that her triglyceride level was elevated and that she should contact her PCP.

3. TSH: If a participant has a TSH out of the normal range at any timepoint she will be contacted and advised to contact her PCP.

d. Adverse event reporting guidelines: The principal investigator is responsible for reporting all adverse events according to guidelines. Expected and unexpected adverse events associated with this protocol will be reported to COMIRB per guidelines. All potential adverse events will be reviewed by the study staff at our weekly meeting.

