Upon signing the consent form and enrolling in this research study, all women will be scheduled for their first of 3 study visits approximately 6 weeks postpartum. The consent form will include language to allow study staff access to the medical record information to confirm medical diagnoses by the inclusion criteria stated above. Subjects who do not have medical conditions as defined by the inclusion criteria stated above documented in their medical records will not be eligible to continue in the study. If a subject becomes pregnant during the course of the study, she will be asked to be followed during the pregnancy to determine occurrence of pregnancy complications and gestational weight gain.

Study Visits

At study visits, all women will be assessed for clinical outcomes, behavioral outcomes, mediating variables, and moderating variables (see table 3). Clinically relevant labs (pregnancy tests, OGTT, fasting glucose, HbA1c, TSH, LDL, triglycerides) will be reviewed when results are available. All subjects will complete approximately 45 minutes of questionnaires at study visits.

In accordance with ADA recommendations and UCH standard of care guidelines for postpartum diabetes screening for patients with prior GDM, which suggest 6 week postpartum glycemic status check via oral glucose tolerance test (OGTT), all enrolled subjects with a history of GDM will be offered an OGTT. Study staff will schedule this visit and with the subject’s permission, share OGTT results with subject’s pregnancy care provider (MD or CNM), thereby eliminating the scheduling of duplicate lab appointments. We anticipate this collaboration with OB caregivers will be welcomed, as published data demonstrate clinicians have a difficult time getting these women in for their 6 week postpartum OGTT – less than 50% of women had a 6 week postpartum OGTT.^[[42]](#endnote-42)^

All subjects will be instructed to arrive fasting to study visits, i.e. nothing except water for 10 hours prior to study visit. At study visits up to 50 cc of blood will be drawn, including fasting bloods and optional blood for storage.

During the first study visit, all enrolled subjects will be randomized using previously described permuted block scheme to either control or intervention arm.

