2) Lifestyle CoachA registered dietitian (RD) with training in patient-centered counseling techniques will work with the participants to help them set and achieve goals. The lifestyle coach will provide feedback, advice, and support through the *Fit After Baby* app, and via text messages and email messages. She will prepare to answer questions related to content for each week, how to use the app, and be available to answer any other questions the participant may want answered.

A study physician trained in patient centered counseling will periodically review email and text interactions, as well as notes from phone calls, to ensure adherence to these techniques. The coach and study physician will view progress of participants through a dedicated portal via an android coaching app where they can track diet, physical activity, weight, and progress towards individualized goals.

After a subject has completed the 12 month visit, we will send results of fasting glucose, lipid profile, hsCRP, HbA1c, and TSH from all study visits. The results will be accompanied by a letter from the study physician.

For women who completed their 6-week visit but do not complete their 6 or 12 month visits, we will attempt to reach them by phone, text, email, and/or mail. Additionally, during the consent process, we will get permission from subjects to contact a family member or friend if we are having trouble getting in touch with the subject at any point in the study.

Study Outcomes:

The primary outcomes are change in weight from baseline to 6 months and to 1 year postpartum (exit study visit), and change in weight from self-reported pre-pregnancy weight to one year postpartum.

Secondary outcomes**:** We will assess engagement and satisfaction with the program as potential mediators, defined as use of the app, adherence to self-monitoring of weight, diet, and physical activity, and interactions with the lifestyle coach. To assess changes in cardiometabolic risk factors we will obtain: blood pressure, waist circumference, and biomarkers at baseline, 6 months, and 12 months. We recognize that some of these measurements will be elevated in the postpartum state, however we hypothesize that we will see a greater change among women randomized to the intervention program. We will also assess sleep adequacy and appetite using scales embedded in the app and also sleep data from the Fitbit.

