Recruitment targets and power calculation: We plan to recruit at least 7 participants per month, with a goal of consenting 140 subjects to account for recruitment yield of 50-70%. After 2 years we should have data from 81 participants at one year postpartum. With 54 subjects in the intervention group and 27 subjects in the control group, a 2-sample t-test controlling for baseline weight will have at least 87% power to detect a 4.2 kg difference between groups in 12 month weight change (the 4.2 kg difference with a pooled standard deviation of 5.7 kg was observed in the Balance after Baby RCT). This is adequate power for a pilot study designed to establish the foundation for a subsequent larger pragmatic trial of the *Fit After Baby* program.

+Structured interviews

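### The LDL call rule rests on a level that includes 190 mg/dL but triggers the call only above 190, so a result of exactly 190 is left out

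*Protocol*

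**What the plan says.** Section 6.1 of the Protocol, under outcomes monitoring, introduces its laboratory rules with "We will address abnormal lab values as follows". Item 2, on the fasting lipid profile, cites a blood cholesterol guideline under which statins should be prescribed to patients without clinical atherosclerotic disease "with a LDL-C above or equal to 190 mg/dL". The same sentence then sets the study's action: "if a subject has a LDL-C above 190mg/dL, the study physician will call the participant". The purpose of the call is to tell the woman that her cholesterol is elevated and that she should contact her PCP.

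Three other statements bear on what happens to a lipid result:

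- Section 6.1, safety monitoring: "A physician reviews all laboratory results as they become available".
- Section 5.6, study visits, on the clinically relevant laboratory tests: "LDL, triglycerides) will be reviewed when results are available".
- The text following the lifestyle coach description: after the 12-month visit, "we will send results of fasting glucose, lipid profile, hsCRP, HbA1c, and TSH from all study visits", with a letter from the study physician.

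None of the three gives an LDL action level. The measurement table schedules the fasting lipid profile at all three visits, also without a threshold.

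**The concern.** The LDL item is an instruction to staff and not background, because it sits in the list that says how abnormal values will be handled. Its reason includes 190 mg/dL and its trigger excludes it. At that one value the protocol's own basis says treatment is indicated, while the call that would send the woman to her PCP is left to the discretion of whoever reviews the result.

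What is at stake is one notification at one value. A woman with 190 at the 6-week visit who was not called would have no stated route to that result until the mailing after the 12-month visit. A woman who never completed that visit would have no stated route at all. No outcome, power figure or analysis depends on the rule.

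**Working it through.** **The two conditions side by side**

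| LDL-C result (mg/dL) | Meets the stated basis (≥ 190) | Triggers the call (> 190) |
|---|---|---|
| 189 or below | no | no |
| 190 | yes | no |
| 191 or above | yes | yes |

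The rules disagree only at 190. The guideline level is taken as the protocol reports it and was not checked against the source.

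**How often this could matter**

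The protocol gives no frequency to reproduce, so the size has to be approximated.

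Inputs from the Protocol:
- 81 women with one-year data (power calculation).
- Three visits with a fasting lipid profile (measurement table).
- The recruitment plan, "with a goal of consenting 140 subjects to account for recruitment yield of 50-70" per cent. This gives 140 × 0.50 = 70 to 140 × 0.70 = 98 women.

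Assumptions, since the Protocol gives no LDL data: results reported as whole numbers, and LDL normally distributed with mean and SD of (115, 30), (120, 35) or (125, 38) mg/dL.

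Probability that one result is reported as 190:

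p = Φ((190.5 − mean)/SD) − Φ((189.5 − mean)/SD)

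- (115, 30): Φ(2.517) − Φ(2.483) = 0.00058
- (120, 35): Φ(2.014) − Φ(1.986) = 0.00154
- (125, 38): Φ(1.724) − Φ(1.697) = 0.00243

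Expected number of such results = 3 × n × p:

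| Women | (115, 30) | (120, 35) | (125, 38) |
|---|---|---|---|
| 70 | 0.12 | 0.32 | 0.51 |
| 81 | 0.14 | 0.37 | 0.59 |
| 98 | 0.17 | 0.45 | 0.71 |

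Chance of at least one among 81 women, treating results as independent, is 1 − (1 − p)^243 = 0.13, 0.31 and 0.45. Repeat results in one woman are correlated. That does not change the expected count and hardly changes the chance of at least one: with a random-intercept model at correlation 0.8 it is 0.13, 0.31 and 0.44.

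A 12-month result goes out in the mailing that follows that visit, so one may prefer to count only the 6-week and 6-month results. For 81 women, 2 × 81 × p = 0.09, 0.25 and 0.39.

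**The case against.** The best defence is that the second figure is shorthand for the first. Both stand in one sentence, and the call rule is expressly based on the inclusive level, so a physician would probably read 190 as included. The neighbouring glucose item is similarly loose: it sets the later-visit HbA1c trigger at 6.5 or more and then speaks of results that exceed these values. The shorthand reading is plausible, and it suggests a slip and not a deliberate exclusion. It does not alter the words of the rule, and the reader cannot tell from the text which was meant.

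A second argument is that the guideline level concerns prescribing, while the study's action is only a phone call, so the two cutoffs need not agree. That is true in principle. But the protocol offers the prescribing level as its reason for calling and gives no reason to leave out 190.

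A third is that oversight is good. A physician reviews all results, and the principal investigator is responsible for reviewing and reporting data within 24 hours of receipt. A result of 190 would therefore be seen promptly, and nothing forbids a call. This softens the practical effect, but neither provision sets an LDL action level or requires the call.

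Finally, the matter is said to be too small to raise. The small size is accepted; it governs the priority of the correction and does not make the wording right.

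**Conclusion.** The point holds as a minor wording error in an operative notification threshold. It rests on the text alone: the stated basis includes 190 mg/dL, the trigger does not, and nothing elsewhere in the Protocol requires a call at that value.

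Fewer than one affected result is expected under every scenario examined, whether two or three visits are counted. That estimate depends on the assumed LDL distributions and whole-number reporting; the mismatch itself does not. The correction is desirable but low in priority.

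**What to change.** In the lipid item of outcomes monitoring, change the trigger so that the study physician calls any participant whose LDL-C is at or above 190 mg/dL, matching the basis given in the same sentence. This takes a few words and can go into the next protocol amendment. On the assumptions used here it adds fewer than one expected phone call over the whole trial. If the sponsor does intend to leave out exactly 190, one clause giving the reason would settle the matter instead.

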7. DATA SAFETY AND SECURITY

A number of measures will be undertaken to ensure that participants’ confidentiality is maintained and that data are secure. These include:

1. Study activities involving human subjects will not begin until approval has been granted from COMIRB.
2. Recruitment and screening data, data from focus groups, discussion threads, and survey data will be stored on a secure server at the University of Colorado.
3. Survey Data Storage: Surveys will be housed on Research Electronic Data Capture (REDCap), a secure site for online data collection that is HIPAA compliant, and links to the surveys sent to participant e-mails.
4. All data collected from participants will be identified by ID number only, and will be encrypted when transmitted from the Internet. At the end of the research study, all data are permanently de-identified for archive, according to the schedule established by COMIRB.
5. All investigators and staff have completed the CITI Basic Course and CITI Health Information Privacy and Security (HIPS) Course.
6. Data collected through the Fit After Baby application and website will be protected via security measures. The dataset will include ID number, email address, and cell phone number (to enable emailing and texting functions), but no other personally identifying information. The security measures include monitoring data, protecting privacy of subjects, and maintaining confidentiality of data. The Data Center (managed by Google, Inc.) has a Global Compliance function that is responsible for legal and regulatory compliance as well as a Global Internal Audit function responsible for reviewing and auditing adherence to compliance requirements, including Sarbanes-Oxley and Payment Card Industry standards (PCI). The security measures include physical measures, access protection, storage protection, network security, measures to protect data transfer, measures to protect against data loss and security breaches, and measures to address disaster recovery and continuity of services.

1) **Physical Security Measures:**

Staff at headquarters are responsible for the physical security of Comprendo’s offices. Google staff and data center facilities are protected with Google’s security officers who are qualified with training to protect high security enterprises with mission-critical infrastructures. The servers feature a Hardware Firewall and run active intrusion monitoring. All access to web portal and any client data is secured over HTTPS using SSL 256-bit encryption. Additionally, it is policy for all staff members with access to participant data to receive training as a HIPAA Privacy Associate, and be trained in HPIAA Privacy Rights.

Google’s data centers are geographically distributed and employ a variety of physical security measures. The standard physical security controls implemented at each Google data center are composed of well-known technologies and follow generally accepted industry best practices: custom designed electronic card access control systems, alarm systems, interior and exterior cameras, and security guards. Access to areas where systems, or system components, are installed or stored are segregated from general office and public areas such as lobbies. The cameras and alarms for each of these areas are centrally monitored for suspicious activity, and the facilities are routinely patrolled by security guards. Google’s facilities use high resolution cameras with video analytics and other systems to detect and track intruders. Activity records and camera footage are kept for later review, should it become necessary. Access to all data center facilities is restricted to authorized Google employees, approved visitors, and approved third parties whose job it is to operate the data center. Google maintains a visitor access policy and set of procedures stating that data center managers must approve any visitors in advance for the specific internal areas they wish to visit. The visitor policy also applies to Google employees who do not normally have access to data center facilities. Google audits who has access to its data centers on a quarterly basis to help ensure that only appropriate personnel have access to each floor. Google restricts access to its data centers based on role, not position. As a result, even most senior executives at Google do not have access to Google data centers.

**2) Access:** All account data are secured by standard https security protocols. Maintenance access is secured by Google Admin Account access and controlled by the Chief Technology Officer of the organization through the use of Web Admin tools. Approval to use these Web Admin tools is provided by the CTO to a limited set of employees based on job responsibilities and position within the organization. A separate development and testing environment will be used to help minimize access to participant data.

**3) Storage:** The architecture is built on the Google Cloud platform and takes advantage of Google's strong security measures and data centers. (<https://cloud.google.com/files/Google-CommonSecurity-WhitePaper-v1.4.pdf>)

**4) Network security:** Google employs multiple layers of defense to help protect the network perimeter from external attacks. Only authorized services and protocols that meet Google’s security requirements are permitted to traverse the company’s network. Unauthorized packets are automatically dropped.

**5) Transport security**: Google provides many services that make use of the Hypertext Transfer Protocol Secure (HTTPS) for secure browser connections. Information sent via HTTPS is encrypted from the time it leaves Google until it is received by the recipient’s computer.

**6) Data Transfer security:** Electronic transmission of Personal Health Information (PHI) or Personally Identifiable Information (PII) over the internet (including by email), file transfers or other data transfer modalities, will be encrypted. The account data is secured by standard https secure protocol (Secure Socket Layer - SSL). No data containing PHI or PII may be sent from or forwarded to an external account such as Gmail, Yahoo mail, etc.

**7) Data Loss/Security Breach:** Examples of security breaches include (1) lost or stolen desktops laptops, USB drives, CD/DVD/Zip Drives, etc. with stored data; (2) a compromised account which is used to look up data (e.g., unauthorized user has had access to the account); (3) a compromised work station or server that contains data; and (4) accidental disclosure or data to unauthorized recipients (e.g., sending data to an incorrect email address). In compliance with HIPAA, it is policy to notify participants alerting them to breaches “without unreasonable delay,” but no later than 60 days after discovery of the breach. Notice to the secretary of Health and Human Services (HHS) and prominent media outlets about breaches involving more than 500 patients.

**8) Disaster Recovery and Continuity of Services:** To minimize service interruption due to hardware failure, natural disaster, or other catastrophe, Google implements a disaster recovery program at all of its data centers. This program includes multiple components to minimize the risk of any single point of failure, including the following: 1) Data replication and backup: application data is replicated to multiple systems within a data center, and in some cases also replicated to multiple data centers. 2) Google operates a geographically distributed set of data centers that is designed to maintain service continuity in the event of a disaster or other incident in a single region. High-speed connections between the data centers help to support swift failover. Management of the data centers is also distributed to provide location-independent, around-the-clock coverage, and system administration. 3) In addition to the redundancy of data and regionally disparate data centers, Comprendo also has a business continuity plan for its headquarters in Santa Barbara, CA. This plan accounts for major disasters, such as a seismic event or a public health crisis, and it assumes people and services may be unavailable for up to 10 days. This plan is designed to enable continued operations of services for customers. Comprendo destroys PHI or PII on request by individuals or covered entities according to HIPAA policies except in exceptional circumstances. Where destruction is not possible the data will be anonymized to the extent possible while maintaining the integrity of the platform, and access to the data will be restricted.

